### **Funding Sources: New Investigator Fund - Hamilton Health Sciences**

## BACKGROUND

The global population is living longer and the number of individuals 65 years and older is estimated to reach 2 billion by 2050 (1). A profound implication of the older adult population is the growing number of individuals that present with frailty. Frailty is a multidimensional syndrome characterized by a decline in function across multiple physiological systems including the cardiovascular, musculoskeletal, neurological, and immunological systems (2,3). When exposed to a stressor (e.g., fall, fracture, urinary tract infection), individuals who are frail are more vulnerable to experience a larger and faster deterioration in their health, which may manifest as functional dependency and the inability to return to baseline function and homeostasis (2). Frailty is an important risk factor for negative health outcomes such as increased falls (6,7), fractures (8), hospitalization (8), disability (8), nursing home admission (9), social isolation (4,10), and mortality (11). Frailty is more common in females than in males but mortality rates due to frailty are higher in males, and its prevalence is influenced by socioeconomic factors (12). It is estimated that approximately 1 in 6 community-dwelling older adults may have frailty and it gets worse with age, with 1 in 2 individuals 85 years and older being frail (13).

Older adults who are frail are more likely to be sedentary (14,15). Sedentary behaviour is defined as any waking behaviour in a standing, seating, or reclining posture, with a low energy expenditure ( $\leq 1.5$  metabolic equivalent of task [METs]) (16). The coexistence of frailty and sedentary behaviour worsens overall health (15). Sedentary behaviour is not merely the absence of moderate or vigorous physical activity but also a reduction in sit-to-stand transitions, stand time, and light physical activity (17). Most older adults who are frail spend more than 60% of their awake time in a seated position, which is equivalent to more than 9.5 hours/day of continuous sedentary behaviour (17). The deleterious health effects of sedentary behaviour are different to

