those of physical inactivity and are partially independent of an individual's physical activity levels (17). Even older adults who meet the recommended aerobic exercise guidelines of moderate to vigorous physical activity might experience adverse effects of sedentary behaviour (17). Thus, interventions to reduce periods of prolonged sedentary behaviour are necessary.

Older adults who are frail are potentially the population that might benefit the most from a reduction in sedentary time as they are the most sedentary group and have the highest chronic disease burden (18). However, there is a dearth of evidence on effective interventions to reduce sedentary behaviour or total sedentary time in older adults, especially among individuals that are frail (15,19,21). Previous studies focused on reducing total sedentary time, while other studies aimed to increase physical activity levels with the assumption that sedentary time will be reallocated to physical activity (21). But, to date, such interventions have not been effective at reducing total sedentary behaviour time in older adults (15). Previous studies to reduce sedentary time and behaviour in older adults may not be effective because there is no research on the context of sedentary behaviour, about when and where to intervene, and which specific sedentary behaviours should be targeted (15,19). Almost all studies in older adults have assessed total sedentary time, which does not provide enough information to understand the context of sedentary behaviours (15,19). The main reason to understand context is because not all sedentary behaviours should be modified as some cognitively engaging sedentary behaviours (e.g., reading, socializing) appear to benefit health, while time spent in more passive activities may be detrimental. Therefore, the goal should not be to reduce total sedentary time, but rather identify sedentary behaviours that may be detrimental to the health of older adults who are frail (21).

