## Outcomes

### *Primary outcome*

The primary purpose of this study was to assess the feasibility of measuring the context of sedentary behaviour among older adults who are frail. We defined feasibility using recruitment, retention, and refusal rates (process) and the feasibility resource (i.e., can the tools capture context and are participants willing to use the tools).

Accelerometer: We will use the activPAL4™ accelerometer to collect data on posture and time of day over three consecutive days in the winter and spring. The activPAL4™ is a valid accelerometer in older adults that generates totals for the time spent lying, sitting, standing, and stepping every second of the day (22). The accelerometer is secured to participant's lower thigh with a 3M Tegaderm Transparent bandage and can hold its charge for up to 14 consecutive days. The accelerometer will not interfere with participants daily lives and can be used in the shower or pool. Data is collected wirelessly and stored on the hard drive of the accelerometer and will be transferred to a secured McMaster cloud by a research assistant.

Indoor Positioning System: We will use a McMaster developed indoor positioning system to obtain room/area level positioning information over three days in the winter and spring. The system is designed and validated to be used by older adults in their own homes without the need for a floor plan and only minimal initial setup and calibration (23). The participants will wear a commercially available, off-the-shelf smartwatch with customized software and plug-n-play ambient (nonwearable) beacons in in different rooms of the participant's homes. The smartwatches are

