### ***Secondary outcomes***

The secondary objectives will be to conduct: 1) focus groups with end-users to identify an intervention on when and where to intervene to breakup or reduce certain types of sedentary behaviour and determine the feasibility of using the indoor positioning system and diary; 2) to determine the context of using objective and subjective measures to assess sedentary behaviours among older adults who are frail; and 3) to conduct an exploratory analysis to determine the association of certain types of sedentary behaviours on health-related outcomes. We will hold two focus groups after the winter and spring collection period to mitigate recall bias. We will use semi-

structured interviews to guide interviews using the Behaviour Change Wheel (25) and the Intersectionality Supplemented Theoretical Domains Framework (26). The purpose of using an intersectional lens is to understand how sedentary behaviour may differ by sex and ethnicity due to gender-constructed norms and cultural differences, respectively. The term intersectionality was coined by professor Kimberlé Crenshaw to describe how gender, race, class, and other individual characteristics “intersect” with one another within structures of power and communities (28). We will also conduct an exploratory analysis to determine the association of certain types of sedentary behaviour on falls, cognition, frailty status, activities of daily living, health-related quality of life, depression, and anxiety (see Table 2).

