#### ***Secondary outcome analysis***

Data analyses from the accelerometer, the indoor positioning system, and participants' diaries will be mapped to the Sedentary behaviour International Taxonomy (SIT) using classification scheme content analysis (37). SIT is a framework developed to help researchers understand the context and determinants of sedentary behaviours. We will post process the data from the accelerometers and indoor positioning system in one-hour intervals. Using posture, we will exclude time intervals related to overnight sleep and walking, and only analyse sedentary behaviours that includes lying, sitting, and standing. Posture, environment, purpose, and social context will be converted to an alphanumeric value based on one of the SIT categories (see Table 4) and we will report the sequences of values as a count/frequency using content analysis. For example, a combination of *lying-bedroom-rest-alone* between 2:30 pm to 3:30 pm would result in a sequence of *P1-E1-U7-S2 in the afternoon*; we will report the most common sequence combinations in the final results.

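### Hourly sequence counts cannot show where sitting or lying is prolonged or already interrupted, although the study is meant to inform when and where to break it up

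*Protocol*

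**What the plan says.** Under Secondary outcome analysis, the Protocol sets the time grid: "We will post process the data from the accelerometers and indoor positioning system in one-hour intervals". Posture, environment, purpose and social context are then turned into codes. The summary is fixed too: "we will report the sequences of values as a count/frequency using content analysis", and "we will report the most common sequence combinations in the final results". Table 4 lists the coded elements. Its time element is clock time and date; no element covers duration or transitions. The exploratory regression takes the same sequences as its exposure.

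The stated purpose goes further than frequency. The Background concludes: "Thus, interventions to reduce periods of prolonged sedentary behaviour are necessary". It also describes the construct in terms of interruption: "Sedentary behaviour is not merely the absence of moderate or vigorous physical activity but also a reduction in sit-to-stand transitions". Under Secondary outcomes, the focus groups are to "identify an intervention on when and where to intervene to breakup or reduce certain types of sedentary behaviour", and the Discussion presents the study as a first step towards such an intervention.

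The instrument can supply what is missing. Under Primary outcome, the accelerometer "generates totals for the time spent lying, sitting, standing, and stepping every second of the day".

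**The concern.** Breaking up sedentary time requires knowing where it is unbroken. A count of hourly codes records how often a context occurs. It does not record how long a person stayed down without getting up, or how often they got up within the hour. Two rooms with equal counts may differ completely in this respect: one may hold long unbroken bouts and the other short bouts already interrupted many times.

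At stake is the breaking-up part of the secondary objective. If the focus groups are shown only the planned counts, they have no quantitative information on which contexts contain prolonged sitting or lying. The counts do give a rough guide to total time, but the Background says that lowering total sedentary time should not itself be the goal.

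**Working it through.** The Protocol gives no figure to reproduce on this point, and no sample-size or power quantity bears on it. The check is whether the planned summary can separate different bout patterns.

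**Inputs from the Protocol.** Hourly grid and count summary (Secondary outcome analysis); posture codes for lying, sitting, standing and other (Table 4); posture recorded to the second (Primary outcome, accelerometer paragraph).

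**Assumptions.** (a) An hour takes the posture that fills more than half of it; the Protocol has no rule for mixed hours. (b) Room, purpose and company stay constant, so only posture varies. (c) The sit/up patterns and the 30-minute cut-off are illustrative and do not come from the Protocol.

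**Method.** Take 10 hours (600 minutes) and repeat a cycle of *s* minutes sitting and *u* minutes up. Then:
- number of bouts = 600 / (*s* + *u*)
- sitting minutes = number of bouts × *s*
- sitting share of each hour = *s* / (*s* + *u*)
- sit-to-stand transitions per sitting hour = number of bouts / (sitting minutes / 60), as each bout ends in an up period (none for continuous sitting)

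| Pattern (sit/up, min) | Sitting share of each hour | Hourly sitting count | Sitting min | Bouts | Longest bout (min) | Min in bouts ≥30 min | Transitions per sitting hour |
|---|---|---|---|---|---|---|---|
| Continuous | 100% | 10 | 600 | 1 | 600 | 600 | 0 |
| 50/10 | 83% | 10 | 500 | 10 | 50 | 500 | 10 / 8.33 = 1.2 |
| 25/5 | 83% | 10 | 500 | 20 | 25 | 0 | 20 / 8.33 = 2.4 |
| 5/1 | 83% | 10 | 500 | 100 | 5 | 0 | 100 / 8.33 = 12 |

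The hourly count is 10 in every row. The last three rows also share the same total sitting time (500 minutes, or 8.33 hours), so total time does not separate them either. Bout length and transition rate do.

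**Other coding rules.** The result does not depend wholly on assumption (a).
- *Drop any hour that contains walking.* The Protocol excludes walking intervals. If the up minutes include walking, the counts become 10, 0, 0 and 0. Continuous sitting now stands apart, but 50/10 and 5/1 still look the same.
- *Code each bout separately.* The counts become 1, 10, 20 and 100, so a ranking by frequency would put the most interrupted pattern first. The Protocol's hourly grid and its one-hour worked example make this reading unlikely.

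None of the three rules yields a table of where long unbroken bouts occur.

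**The case against.** The strongest reply is that the analysis matches the objective as defined. Objectives and Aims defines context as purpose, location, posture, social setting and time of day, and Table 4 covers these. Bout length is not in that definition, prolonged sitting belongs to the rationale, and breaking up is named as an alternative to reducing. This has force: the counts do serve the definition of context and part of the reducing aim. But breaking up is written into the secondary objective as well as the Background, and no planned result addresses it.

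A reader might infer that the study cannot locate prolonged sitting at all. The Protocol does not support that. The second-level record would allow bouts to be derived, and successive identical hourly codes give a coarse hint of persistence, although no analysis of runs is planned and breaks within the hour stay hidden.

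A reader might also infer that ranking by frequency will send the intervention to the wrong place. The Protocol has no such decision rule. Focus groups, analysed with the Behaviour Change Wheel, identify the target, and under Study Design they review results from all three instruments.

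Nor should the volume of data be read as the size of an error. The Background figure of 9.5 hours a day gives 9.5 × 3 days × 2 seasons × 20 participants = 1,140 hours. That describes the record under full retention and complete wear, and posture from it is used for the coding.

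Two practical objections stand and shape the fix. The diary has no stated time resolution, so bouts may not be assignable to a purpose or social setting. And the Protocol counts standing as sedentary, so a sit-to-stand transition does not end a sedentary period on its own definition.

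Finally, a statistical analysis plan, not available here, could add bout measures. The point is still more than a missing detail, because the Protocol itself fixes an hourly grid and a count summary that do not fit part of its stated aim.

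**Conclusion.** The concern holds for the planned results. As written, they approximate total time in each context but cannot show where sitting or lying is prolonged or already interrupted. Under majority-posture coding, longest bouts from 5 to 600 minutes all give the same count of 10 sitting hours. That illustration rests on an assumed coding rule and constructed patterns; it shows what the summary cannot distinguish and does not predict the data. The consequence is limited to the breaking-up part of a secondary objective in a feasibility study of 20 participants. Recruitment, retention, refusal and the feasibility of the tools are unaffected. The change is worth making because the data are already to be collected.

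**What to change.** Keep the sequence counts. Add to Secondary outcome analysis, from the accelerometer and positioning records:

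1. the length of each uninterrupted sitting/lying bout;
2. sit-to-stand transitions per sitting/lying hour;
3. the share of waking sitting/lying time spent in long bouts, with cut-offs fixed before analysis (30 and 60 minutes would be examples only).

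Summarise each measure within participant first, then tabulate by room and time of day. Add purpose and social context only where the diary's time resolution allows a bout to be matched to an entry. State that these measures cover sitting and lying only, because the Protocol otherwise codes standing as sedentary. Bring the tables to the focus groups alongside the counts.

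The cost is a modest amount of extra processing. No new data, visits, devices or participants are needed.

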**Table 4: Details on how, when, and where sedentary behaviour will be mapped**

| Primary outcome                | SIT Categories to assess primary outcome (37) | Category Details and sequence codes                                                                           | Data Collection Instrument                      |
|--------------------------------|-----------------------------------------------|---------------------------------------------------------------------------------------------------------------|-------------------------------------------------|
| Context of sedentary behaviour | Posture                                       | Lying (P1), sitting (P2), standing (P3), other (P4)                                                           | Accelerometer                                   |
|                                | Environment                                   | Bedroom (E1), kitchen (E2), living room/common area (E3), eating area (E4), other (E5)                        | Indoor Positioning System                       |
|                                | Purpose                                       | Work (U1), leisure (U2), education (U3), travel (U4), social (U5), eat (U6), rest (U7), care (U8), other (U9) | Diary                                           |
|                                | Social Context                                | With others (S1), alone (S2)                                                                                  |                                                 |
|                                | Measurement                                   | Objective or self-report                                                                                      | Accelerometer, Indoor Positioning System, Diary |
|                                | Time                                          | Time of day and date                                                                                          |                                                 |

We will analyze focus group interviews using codebook reliability thematic analysis in Nvivo12 Pro software (QSR International PTY Ltd, Doncaster, Australia). Codes are developed *a priori* from an existing framework, and we will use the Behaviour Change Wheel, which is a commonly used framework to inform interventions and policy changes (25). This framework posits that Capability, Opportunity, and Motivation govern Behaviour (COM-B) (25). Two members of the research team will transcribe and analyze the interviews and classify each theme under a relevant category of COM-B, applying more than one category if needed. The results of focus groups will identify an intervention function and policy change in the Behaviour Change Wheel (See Appendix B).

We will conduct an exploratory analysis of secondary outcomes using multiple linear regression in SPSS Statistics version 27 (IBM Corp, Armonk, New York, USA). Our independent variable will be the most common sequences of sedentary behaviour (e.g., *P1-E1-U7-S2*), and our dependent variable will be the secondary health outcomes (e.g., frailty level, cognitive status). Our covariates will include variables from PROGRESS (i.e., age and sex).

### **Trial Management and Staff Training**

The study central site is at St. Peter's Hospital in Hamilton, ON. The central research assistant and principal investigator will be responsible for ethics, recruitment, and day-to-day trial management. The principal investigator will provide training to the research assistant on how to consent potential participants and collect outcomes (e.g., review the Standard Operating Procedures of each outcome).

### **Participant Retention and Withdrawal**

Once the participant is enrolled, we will make every reasonable effort to follow the participant for the entire study period. The target retention rate will be 85%. Participants may withdraw from

the study for any reason at any time. The principal investigator may also withdraw participants from the study to protect their safety.

## **Data Management**

### *Data Forms*

A research assistant will create all data collection forms using an editable Portable Document Format (PDF). All editable PDFs will be de-identified and we used the participant's assigned ID (e.g., MAPS001, MAPS002).

### *Data Entry*

Data will be entered and managed electronically on an editable PDF, which will be password protected and kept on a secure network system. The MoCA will be completed by the participant using a paper copy and stored at St. Peter's Hospital in a locked cabinet in a locked room that only the lead investigator and research assistant can access. The research assistant will be responsible for entering diary information and secondary outcomes into the editable PDF.

## **Adverse Events**

We will collect adverse events at two times points: during the winter and spring collection periods. We anticipate that the adverse events will not related to the study.

## **DISCUSSION**

Our study is unique because it will be the first study to utilize objective and self-report tools including accelerometers, indoor positioning systems, and diaries to provide context of sedentary behaviours among older adults who are frail. The proposed project is the first step to inform the co-design of an intervention to reduce or breakup sedentary behaviours and may have

enormous economic and social impacts as older adults living with frailty are the highest-cost users of our healthcare system.

**Appendix A: Proposed Study Timeline**

|                                                                                                  | Pre-rollout |      | Rollout |     |     |      |     |     |       |     |     | Data analysis and dissemination |     |      |
|--------------------------------------------------------------------------------------------------|-------------|------|---------|-----|-----|------|-----|-----|-------|-----|-----|---------------------------------|-----|------|
| Time in months (2022 to 2023)                                                                    | 2022        |      |         |     |     | 2023 |     |     |       |     |     |                                 |     |      |
|                                                                                                  | Aug         | Sept | Oct     | Nov | Dec | Jan  | Feb | Mar | April | May | Jun | Jul                             | Aug | Sept |
| Principal investigator meets with patient partners from the Hamilton Council on Aging            |             |      |         |     |     |      |     |     |       |     |     |                                 |     |      |
| Research assistant develops protocol and study materials                                         |             |      |         |     |     |      |     |     |       |     |     |                                 |     |      |
| Research assistant completes and submits HiREB application                                       |             |      |         |     |     |      |     |     |       |     |     |                                 |     |      |
| Research assistant and collaborators recruits participants                                       |             |      |         |     |     |      |     |     |       |     |     |                                 |     |      |
| Research assistant collects Winter outcomes                                                      |             |      |         |     |     |      |     |     |       |     |     |                                 |     |      |
| Two members of the research team analyses primary outcome (winter)                               |             |      |         |     |     |      |     |     |       |     |     |                                 |     |      |
| Principal investigators holds focus group with research participants and patient partners        |             |      |         |     |     |      |     |     |       |     |     |                                 |     |      |
| Research assistant collects summer outcomes                                                      |             |      |         |     |     |      |     |     |       |     |     |                                 |     |      |
| Two members of the research team analyses primary outcome (summer)                               |             |      |         |     |     |      |     |     |       |     |     |                                 |     |      |
| Principal investigators holds second focus group with research participants and patient partners |             |      |         |     |     |      |     |     |       |     |     |                                 |     |      |
| Research team analyzes final results and completes manuscript for publication                    |             |      |         |     |     |      |     |     |       |     |     |                                 |     |      |

**Figure A1:** Study timeline for the mapping sedentary behaviour project
